## **4.2 Responsibilities**

Principal Investigator (PI):

Checking for AEs

1. Using medical judgement in assigning seriousness and causality
2. Ensuring that all SAEs are recorded and reported to WCTU (to receive on behalf of the Sponsor) within 24 hours of becoming aware of the event and provide further follow-up information as soon as available. Ensuring that SAEs are chased with WCTU if a record of receipt is not received within 2 working days of initial reporting.

3. Ensuring that AEs are recorded and reported to WCTU (to receive on behalf of the Sponsor) in line with the requirements of the protocol.

Chief Investigator (CI)/delegate or independent clinical reviewer:

1. Clinical oversight of the safety of patients participating in the trial, including an ongoing review of the risk / benefit.
2. Using medical judgement in assigning causality review of any specific SAEs in accordance with the trial risk assessment and protocol as detailed in the Trial Monitoring Plan.
3. Production and submission of annual reports to the REC.

Sponsor or delegate:

1. Central data collection and verification of AEs and SAEs, according to the trial protocol.
2. Expectedness assessment of related SAEs.
3. Reporting safety information to the CI, delegate or independent clinical reviewer for the ongoing assessment of the risk/benefit according to the Trial Monitoring Plan.
4. Reporting safety information to the independent oversight committees identified for the trial (Data Monitoring Committee (DMC) and/or Trial Steering Committee (TSC)) according to the Trial Monitoring Plan.
5. Expedited reporting of related and unexpected SAEs to the REC within required timelines.
6. Notifying Investigators of related and unexpected SAEs that occur within the trial.

Trial Steering Committee (TSC):

In accordance with the Trial Terms of Reference for the TSC, periodically reviewing safety data and liaising with the DMC regarding safety issues.

Data Monitoring Committee (DMC):

In accordance with the Trial Terms of Reference for the DMC, periodically reviewing unblinded overall safety data to determine patterns and trends of events, or to identify safety issues, which would not be apparent on an individual case basis.

### **4.3 Notification of deaths**

Death is collected as a study outcome. No separate notification of death is required.

#### **4.4 Reporting urgent safety measures**

If any urgent safety measures are taken the CI/Sponsor shall immediately, and in any event no later than 3 days from the date the measures are taken, give written notice to the relevant REC of the measures taken and the circumstances giving rise to those measures.

## **5 DATA MANAGEMENT**

### **5.1 Data collection and management**

We will use the standard CTU study web-based application for study management and to record participant data (including case report forms) in accordance with the protocol. Clinical data will be collected during the ICU stay up to 30 days after randomisation or hospital discharge, whichever is later. Baseline characteristics collected include patient demographics, comorbidities, pre-admission function, inclusion/exclusion criteria, consent, time and date of randomisation, temperature at hospital admission, and COVID-19 diagnosis status. Data captured following randomisation will include initial device settings, duration of ventilation, prone therapy, ICU/hospital admission status, patient observations, AEs (treatment failure, need for other treatments, renal function, renal replacement therapy), survival status. Confirmation of COVID-19 diagnosis at any point will be recorded. Ethnicity, socioeconomic status and mortality will be reported from hospital records up until discharge and tracked after discharge using NHS Digital, the ICNARC and Research Centre and equivalent NHS data linkage in the devolved nations. ICU and hospital length of stay will be obtained from local centres or data linkage if appropriate.

The case report form (CRF) has been developed by the CTU and made available to the participating sites as a paper and electronic CRF (eCRF) for ease of data collection; supporting materials will be available to staff. All documents will be stored safely in confidential conditions. On all trial-specific documents, other than the signed consent, the participant will be referred to by a unique trial-specific number/patient identifier/code in any database, not by name. The trial will be conducted in accordance with the current approved protocol, Good Clinical Practice (GCP), relevant data protection regulations and standard operating procedures (SOPs). A monitoring plan and risk assessment will be devised to protect participant safety and integrity of trial data.

### **5.2 Database**

The database has been developed by the Programming Team at WCTU and all specifications (i.e. database variables, validation checks, screens) agreed between the programmer and appropriate trial staff.

### **5.3 Data storage**

All essential documentation and trial records will be stored by WCTU in conformance with the applicable regulatory requirements and access to stored information will be restricted to authorised personnel.

### **5.4 Data access and quality assurance**

All data access will be controlled by generic usernames and passwords, and any changes to data will require the user to enter their username and password as an electronic signature in accordance with regulatory requirements. Staff will have access restricted to the functionality and data that are appropriate for their role in the study.

### **5.5 Archiving**

Trial documentation and data will be archived for at least ten years after completion of the trial. Trial Master File and associated data will be archived by WCTU; trial data generated at study sites will be archived according to local policy.

## **6 STATISTICAL ANALYSIS**

### **6.1 Power and sample size**

The maximum total sample size will be 4002 patients over the three intervention arms (1334 per arm).

The primary end point will be a binary composite outcome of intubation or mortality within 30 days. An event (1) will be defined as intubation or death and an event (0) will be defined as no requirement for intubation and alive.

In a systematic review and meta-analysis to evaluate the evidence for the use of HFNO against usual care in ARF, the rate of mortality was 8.1% (90/1106) on the usual care arm and the rate of intubation was 15.7% (204/1300). A large UK based multi-centre open-labelled randomised control trial (3CPO) of 1069 patients presented with severe acute cardiogenic pulmonary oedema at 26 emergency department, compared standard oxygen therapy, CPAP and NIV, found a 7 day mortality rate of 9.8% and a mean intubation rate of 2.9% on the standard care arm. This is similar to the intubation rates of 2.7% reported in the British Thoracic Society's *National Respiratory Audit Programme Annual Report 2011/12*. In a large systematic review and cost-effectiveness evaluation of pre-hospital NIV for ARF, the intubation rate on usual rate ranged from 4.6%-17.7% and mortality at 30 days was found to be 9.3%-12.8%. In relation to COVID-19 infection, a very

recent publication in the Lancet using WHO data on the cumulative number of deaths to March 1, 2020, mortality rates were reported to be 5·6% (95% CI 5·4–5·8) for China and 15·2% (12·5–17·9) outside of China. Furthermore, in another study relating to the COVID-19, which assessed, lopinavir- ritonavir and standard care, in hospitalised adults with confirmed SARS-Cov-2 infection and with an oxygen saturation of  $\leq 94\%$ , the mortality rate on standard care at day 28 was 25%.

In our sample size calculation, we have assessed both outcome measures and taken the largest in terms of the incidence, to ensure we have maximum power and sample size for our study. Therefore taking the data from Baud *et al* to be representative of usual care and assuming a conservative incidence of 15% for the composite outcome of intubation or mortality on the usual care arm, then using a two-sided 5% significance level, a total 3000 patients (1000 per arm across 3 arms) would give approximately 90% power to detect an odds ratio of 0.625, corresponding to a reduction from 15% to 10% in the composite event rate. allowing for the 11 interim analyses. Our comparisons will be based on CPAP versus standard care and HFNO versus standard care and allow for the formal interim analyses as agreed with the DMC.

However, there remain many uncertainties regards the sample size parameters and also whether an equal randomisation allocation ratio will be maintained. For this reason we have inflated our sample size to 4000 patients (4002 across the three arms) to maintain the study power and detect small effect sizes, if they exist. It may allow us to also assess the difference between CPAP and HFNO, if difference between these interventions are small enough to be detected with this larger sample size. Furthermore, it may be likely that we will not need all these patients if the trial stops at a formal interim analysis or if the DMC recommends that an arm is dropped.

The formal stopping rules will be set out in the statistical analysis plan, following discussions with the DMC. These criteria will be used to accept or drop an intervention arm, based on the assessment of the primary outcome at each interim point.

## **6.2 Statistical analysis of efficacy and harms**

### **6.2.4 Statistics and data analysis**

The statistical analysis will be based on intention to treat and will be conducted in line with the CONSORT statement. For the overall analyses, numbers of events will be assessed using the logistic regression unadjusted and adjusted for important predictors, such as previous morbidities, age and gender) and results will be presented using odds ratios (with 95% confidence intervals). At the interim stages, the numbers of events will be analysed using the latter methods and compared

to the p-value critical values. A final p-value and treatment effect estimate will be calculated adjusting for the interim analyses using the methods described by Jennison and Turnbull, Fairbanks and Madsen and, Emmerson and Fleming. Intubation rates and mortality at 30 days will be assessed using the logistic regression models (both for adjusted and unadjusted analyses) and summarised using odds ratio (with 95% confidence intervals). Continuous secondary data will be presented using summary statistics and analysed using parametric or non-parametric methods depending on the distribution of the data.

If possible, we will conduct a compliers average cause effect (CACE) analysis to assess the effect on the non-compliance to the allocation interventions (for all three interventions or two, if one is dropped).

We anticipate no or very little missing data. However, in the case of missingness, we will use multiple imputation techniques (ICE procedures) to assess the missingness mechanisms.

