## **2.9 Randomisation**

### **2.9.1 Randomisation**

In this trial, there may well be the possibility that the devices will not be available as a result of the challenging environment the clinical staff are presented with. For this reason, we will set up two randomisation systems, which will be integrated to maintain balance.

Prior to randomisation, the clinician/nurse will check the availability of the devices. If no device is available then there will be no randomisation. If one of the devices is available (either CPAP or HFNO), then the clinician/nurse will choose the randomisation procedure which allocates standard care and CPAP or HFNO (system 1). If both devices are available, then system 2 will allow for an allocation using the three arms (standard care, CPAP or HFNO). These two systems will be integrated and constantly updated to ensure that the allocation ratio (1:1:1 for standard care: CPAP: HFNO) is maintained if possible. There is a possibility that this ratio will not be maintained and this has been compensated for in our sample size, which has been inflated accordingly.

A simple and secure, interactive voice response (IVR) randomisation system has been established by the programming team at Warwick Clinical Trials Unit. A computer-generated randomisation sequence has been generated by the minimisation method. Patients will be stratified by site, gender (M/F), and age (<50, >=50 years). If a patient has been randomised and found to be ineligible or the device is not available, they will be included in the analysis on an intention-to-treat basis. Any data already collected will be retained and included in the analysis unless otherwise indicated.

A back-up emergency randomisation system is currently being developed and full details will be made available and maintained on the trial website.

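### The primary outcome has two logistic models and neither is named as the one that decides; site and randomisation system, which shape the allocation, are not named as adjustment factors

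*Protocol*

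**What the plan says.** Section 6.2.4 of the protocol analyses the primary outcome by logistic regression, "assessed using the logistic regression unadjusted and adjusted for important predictors, such as previous morbidities, age and gender". For the interims, "the numbers of events will be analysed using the latter methods and compared" with critical p-values. It then promises one final p-value and one treatment effect estimate, corrected for the interim looks, without naming the model they come from. The formal stopping rules are left to the SAP (section 6.1).

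Section 2.9.1 allocates by minimisation: "Patients will be stratified by site, gender (M/F), and age (<50, >=50 years". It also sets up two linked systems. When both devices are available, patients are allocated among three arms. When only one is available, they are allocated between that device and standard care. The systems are integrated to keep the overall ratio at 1:1:1 if possible.

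Section 6.1 plans two pairwise comparisons with standard care and claims "approximately 90% power to detect an odds ratio of 0.625, corresponding to a reduction from 15% to 10% in the composite event rate" with 1000 patients per arm, "allowing for the 11 interim analyses".

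**The concern.** Three things are at stake.

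- **Which result decides.** One set of critical values and one final estimate cannot serve two models unless one is designated. The two odds ratios are also different quantities. The planned change from 15% to 10% is a marginal contrast, whereas an adjusted logistic model estimates a conditional one.
- **Allocation factors.** When allocation is balanced on a prognostic factor and the analysis ignores it, the standard error is too large for the design. The test becomes conservative and loses power. Age and gender are among the example covariates; site is not named.
- **Randomisation system.** A standard-care patient randomised when only HFNO was available could never have received CPAP. If such patients differ in risk, pooling them into the CPAP comparison compares unlike groups, so an analysis that ignores the system can be biased as well as less precise.

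**Working it through.** **1. The plan's own power.** Inputs from section 6.1: 15% v 10%, n = 1000 per arm, two-sided 5%. With the pooled variance under the null,

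power = Φ[(0.05 − 1.96·√(2·0.125·0.875/1000)) / √((0.15·0.85 + 0.10·0.90)/1000)] = Φ[(0.05 − 0.02899)/0.01475] = Φ(1.425) = 92.3%.

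The Wald test on the log odds ratio gives 91.9%. With 11 or 12 equally spaced analyses, O'Brien-Fleming-type bounds give 91.4% and Pocock-type bounds 84.2 to 84.5%. The stated figure of about 90% is therefore reproduced if O'Brien-Fleming-type bounds are assumed. It is the power of an unadjusted test.

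**2. Unadjusted against adjusted.** One comparison was simulated with 1000 per arm, 40 sites (section 6.2.5), exact balance within site, a single look and marginal rates of 15% v 10%. The protocol gives no site or covariate effects, so the standard deviations (SDs, logit scale) are assumptions.

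| Site SD | Covariate SD | Runs | Unadjusted | Adjusted, no site | Adjusted with site | Loss, unadjusted v with site |
|---|---|---|---|---|---|---|
| 0 | 0 | 2000 | 92.35% | 92.05% | 92.50% | 0.15 (noise) |
| 0.3 | 0.5 | 5000 | 92.80% | 93.40% | 93.84% | 1.0 |
| 0.3 | 0.5 | 2000 | 92.00% | 92.90% | 93.65% | 1.7 |
| 0.5 | 0.75 | 2000 | 92.55% | 93.65% | 94.70% | 2.2 |
| 0.5 | 1.0 | 2000 | 92.50% | 94.80% | 95.25% | 2.8 |
| 0.8 | 1.0 | 2000 | 91.95% | 94.00% | 95.35% | 3.4 |

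Leaving out site alone accounts for about 0.4 to 1.4 points of the loss. Monte Carlo standard error is about 0.3 to 0.6 points.

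A second simulation used a weaker effect (odds ratio 0.66), site SD 0.5 to 0.8 and an age effect of 0.6 to 0.8 per SD. Unadjusted power was 82.8% and 81.4% in its two settings; with fixed site terms it was 85.8% and 86.6%. The fixed-site test had a size of 5.76%. Moving its critical value from 1.899 to 1.960 lowers its power to about 84.4% and 85.2%, leaving gaps of 1.6 and 3.8 points. Together the two simulations give roughly 1 to 4 points.

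**3. Type I error.** In the first simulation, with site SD 0 to 1.0:

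- unadjusted: 3.8 to 5.4%, and 3.8 to 4.3% at the strongest site effects (SD 0.8 and 1.0);
- adjusted without site: 3.9 to 5.0%;
- rejecting if either of these two rejects: 4.9 to 6.3%, so at most 6.3 − 5.0 = 1.3 points above nominal.

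The two models disagree in about 0.3 to 3.6% of simulated trials. In the second simulation the either-rejects rate was 6.1 to 6.2%, but the fixed-site model alone accounted for 5.76%, so the second p-value added only about 0.4 points.

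**4. Randomisation system.** Assume no treatment effect. Half the patients have both devices available (1:1:1, 13% risk) and half have HFNO only (1:1, 17% risk).

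- Standard care: ½·⅓ = 0.167 of patients at 13% and ½·½ = 0.25 at 17%, so risk = (0.167·0.13 + 0.25·0.17)/0.417 = 15.4%.
- CPAP: 13.0%.
- Odds ratio = (0.13/0.87)/(0.154/0.846) = 0.82.

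Varying the assumptions:

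- HFNO-only share of 20%: these patients make up 0.10/(0.10 + 0.267) = 27% of standard care, whose risk is 14.1%, and the odds ratio is 0.91.
- Risks swapped: CPAP 17.0%, standard care 14.6%, odds ratio (0.17/0.83)/(0.146/0.854) = 1.20.
- Equal risks, or no HFNO-only patients: odds ratio 1.
- Overall 1:1:1 restored by rebalancing within the both-device group (HFNO-only still 1:1): standard care is 0.25 at 17% and 0.083 at 13%, risk 16.0%, odds ratio (0.13/0.87)/(0.16/0.84) = 0.78. Integrating the systems therefore does not remove the problem.

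**The case against.** Much of this can properly sit in the SAP, which is not available here. The protocol already sends the stopping rules there, and the full covariate list and choice of decision model commonly go with them. Three stronger readings also suggest themselves, and the documents do not support them.

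- **That the adjusted model leaves site out.** The covariates are introduced as examples, so site is unnamed but not excluded.
- **That two p-values are tested against one boundary by rule.** The reference to the latter methods at the interims can be read as the adjusted model alone, and the final p-value is singular. Testing both is a possible consequence of loose wording; the plan does not state it.
- **That the trial is underpowered because of this.** The stated power was worked out for an unadjusted test and is reproduced by one. The maximum of 1334 per arm adds a third to the 1000 used in that calculation.

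These points stand and limit the concern. If the gap were only the undesignated model, it would be close to a missing detail. What remains is that section 6.2.4 does specify an analysis, and specifies it as a pair. Nothing in it ties the decision to the factors and systems that section 2.9.1 uses to allocate patients.

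**Conclusion.** The point holds in a limited form. The protocol does not say which model decides, and it does not name site or randomisation system for adjustment. An unadjusted decision test would be mildly conservative (size about 4 to 5%) and would give up roughly 1 to 4 power points against a model with the allocation factors, or nothing if those factors are not prognostic. It would not fall materially below the stated 90%, given O'Brien-Fleming-type bounds. If either p-value could decide, the inflation is about 1 point, with 1.3 the largest simulated.

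The possible bias from the randomisation system matters more in kind, but its size and direction are unknown. They depend on how many patients enter when only one device is available and on how their risk differs, and the protocol gives neither. The odds ratio of 0.82 shows the mechanism and is not a forecast.

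The simulations assume a single look and exact balance within site. They fitted site as fixed terms, whose size reached 5.6 to 5.8% in some settings, so part of the apparent power gain reflects that. A random site intercept was not simulated.

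**What to change.** State one decision model for every interim and for the final analysis: logistic regression adjusted for the minimisation factors (site, preferably as a random intercept, gender and age) and for randomisation system. Compare each device only with standard-care patients who could have been allocated to it. Make the unadjusted analysis supportive and never compare it with the boundary.

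The cost is wording in the protocol or SAP, plus carrying the randomisation system into the analysis data set. There are two modest downsides. Each comparison loses the standard-care patients who could not have received that device, though they carry no randomised information about it. The odds ratio also becomes conditional, so report a marginal risk difference beside it, which speaks directly to the planned change from 15% to 10%.

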## **2.4 Outcome measures**

### **2.4.1 Efficacy**

- *Primary*

The primary outcome is a composite outcome comprising intubation or mortality within 30 days. If necessary, patients will be followed up to ascertain all-cause mortality rates at 30 days, using NHS Digital, the Intensive Care National Audit and Research Centre (ICNARC) and equivalent NHS data linkage in the devolved nations. Intubation will be obtained from hospital data.

- *Secondary outcomes*

Secondary outcomes relating to effectiveness include:

- Intubation rates
- Time to intubation
- Duration of invasive ventilation
- Time to death (mortality)
- Mortality in critical care (level 2/3)
- Mortality in hospital stay
- Mortality at 30 days
- Admission to ICU
- Length of stay in critical care (level 2/3)
- Length of stay in hospital

All secondary outcomes will be obtained from hospital records and data linkage where appropriate.

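### Ventilation duration and the two lengths of stay are to be compared as ordinary continuous data, although death ends them and ventilation time exists only in intubated patients

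*Protocol*

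**What the plan says.** Section 2.4.1 of the protocol lists among the secondary outcomes "Duration of invasive ventilation", length of stay in critical care, and "Length of stay in hospital". Section 6.2.4 names two kinds of analysis for effectiveness outcomes. Logistic regression is used for the composite, for intubation and for 30-day mortality. For the rest it says: "Continuous secondary data will be presented using summary statistics and analysed using parametric or non-parametric methods depending on the distribution of the data". It also states: "The statistical analysis will be based on intention to treat".

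The protocol gives no rule for how a patient who dies, is never intubated or is never admitted to critical care enters the three durations. Table 2 in section 3.1 sets follow-up to the later of day 30 and hospital discharge, so hospital stay normally ends in an observed discharge or death.

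**The concern.** A short hospital stay can mean early recovery or early death. A t-type or rank-type comparison of raw days treats the two alike, and checking the distribution does not help, because the problem lies in what the number means and not in its shape. The trial's hypothesis (section 1.3) is that the devices reduce intubation and/or mortality. The arms are therefore expected to differ in the very events that end these durations or decide who has one.

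Ventilation duration has a second difficulty. Comparing it among intubated patients compares subsets formed after randomisation by a component of the primary outcome. The background and rationale (sections 1.1, 1.2 and 1.4) stress critical-care capacity and ventilator demand, so readers will look to these outcomes. What is at stake is their interpretation; the primary result is not affected.

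**Working it through.** **The plan's own figure.** The protocol gives no figure for these durations. Its only power statement (section 6.1, about 90% for 15% versus 10% with 1000 per arm) concerns the composite. It comes out at 92.3% for a fixed design, and at 91.5% with 12 looks under an assumed O'Brien-Fleming-type boundary. It has no bearing on this point.

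**Ventilated subset.** Inputs are the planned composite rates of 15% and 10% and 1334 patients per arm (section 6.1). The composite includes deaths without intubation, so the intubated share cannot exceed it:
- standard care: at most 0.15 × 1334 ≈ 200 patients
- device arm: at most 0.10 × 1334 ≈ 133 patients

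At least 85% and 90% of the arms have no ventilation duration.

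**Shift in mean stay when only mortality differs.** Let m_C and m_T be mortality on standard care and device, and D and S the mean stays of patients who die and who survive, the same in both arms. Then

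mean stay = m·D + (1 − m)·S, and shift (device − standard) = (m_T − m_C)·(D − S).

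Assumption: stays are log-normal with log SD 0.8, so mean = median × exp(0.8²/2) = median × 1.377. Medians are assumed because the protocol gives none.

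For mortality of 15% versus 10% and medians of 7 and 14 days: D = 9.64 and S = 19.28; shift = (−0.05) × (9.64 − 19.28) = +0.48 day.

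The first mortality pair uses the planned composite rates as mortality. The second starts from the 25% day-28 mortality on standard care in the cited COVID-19 drug trial (section 6.1) and assumes a fall to 17.5%. The simulation used 1334 per arm, 500 runs per row and a two-sided Mann-Whitney test at 5% on raw stay.

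| Mortality | Median stay, died / survived (days) | Shift by formula (days) | Simulated shift (days) | Runs with device stay significantly longer |
|---|---|---|---|---|
| 15% vs 10% | 7 / 14 | +0.482 | +0.463 | 17% |
| 15% vs 10% | 5 / 14 | +0.620 | +0.549 | 27% |
| 15% vs 10% | 7 / 21 | +0.964 | +0.947 | 27% |
| 15% vs 10% | 10 / 14 | +0.275 | +0.237 | 6% |
| 15% vs 10% | 14 / 14 | 0 | −0.014 | 2% |
| 15% vs 10% | 20 / 14 | −0.413 | −0.381 | 1% |
| 25% vs 17.5% | 7 / 14 | +0.723 | +0.741 | 31% |
| 25% vs 17.5% | 5 / 14 | +0.930 | +0.905 | 54% |
| 25% vs 17.5% | 7 / 21 | +1.446 | +1.451 | 62% |
| 25% vs 17.5% | 10 / 14 | +0.413 | +0.432 | 11% |
| 25% vs 17.5% | 14 / 14 | 0 | −0.005 | 2% |
| 25% vs 17.5% | 20 / 14 | −0.620 | −0.629 | 1% |

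Where patients who die have the shorter stay, the life-saving arm is significantly shorter on raw days in at most 1% of runs. With deaths given the worst rank in the same data, that arm is significantly favoured in 57–65% of runs (15% versus 10%) and 90–93% (25% versus 17.5%). That reversal reflects the mortality difference itself, since survivors' stay was left unchanged. It shows that the scoring of death can decide the direction of the result.

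**The case against.** The strongest reply is that the handling of deaths in durations is usually settled in the SAP, which was not available for this review. That stands for missing detail. It does not fully answer the point, because section 6.2.4 does state a rule, and the criterion it fixes is the wrong one for these outcomes. Section 6.1 hands the stopping rules to the SAP explicitly; section 6.2.4 makes no such deferral here.

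Three further replies stand:
- Mean days over all randomised patients, deaths included, is a legitimate measure of beds used. A longer mean because more patients survive is then a real difference. The caution is only that it should not be read as harm or benefit to patients.
- The sign is not known from the protocol. It depends on whether patients who die stay for less time than survivors.
- These are secondary outcomes, and 30-day mortality has its own logistic regression, so a survival gain would be reported beside a longer stay.

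A reader might also infer that "Time to intubation" and time to death are to be compared as plain continuous values. The protocol does not say so. It never calls them continuous, and its wording does not exclude Kaplan-Meier or log-rank methods. A short time to either event is unfavourable, so the mechanism above does not apply, and their survival method can be set in the SAP. Nor does the point reach mortality in critical care. That outcome is binary, the quoted sentence does not govern it, and no denominator limited to admitted patients is stated.

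**Conclusion.** The point holds for three outcomes: ventilation duration, critical-care stay and hospital stay. As written, section 6.2.4 compares them by a method chosen on distribution alone, mixing days ended by death with days ended by recovery. For ventilation it leaves open whether the comparison is confined to an intubated subset of at most about 15% versus 10%.

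The size is modest and conditional. It is about +0.5 day at 15% versus 10% mortality with assumed medians of 7 and 14 days. Across the scenarios in which patients who die have the shorter stay, the simulated shift runs from +0.24 to +1.45 days. It is nil at equal stays and negative if patients who die stay longer. It would be too strong to say that the comparison is biased whenever mortality differs: a shift needs different stays in patients who die and survivors, and raw days remain valid for bed use. The primary outcome is not touched.

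**What to change.** Amend section 6.2.4, or state in the SAP before unblinded data are seen:
- **Critical-care and hospital stay:** time to discharge alive, with death as a competing event. State how patients never admitted to critical care are counted.
- **Ventilation:** ventilator-free days to day 30 in all randomised patients, with death scored 0.
- **Raw days:** a descriptive bed-use summary only, shown by survival status.

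The cost is wording. Sections 3.1 and 5.1 already provide for survival status, ventilation duration, and ICU and hospital length of stay. The drawback is that a composite or competing-risk measure is less direct to read than mean days, which is why the raw summary should stay alongside it.
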